## Intervention

### Explanation for the choice of comparators

Not applicable as we did not choose any comparators.

### Intervention description

Measures within the CovidCare-module include patient intake, an initial assessment and several telephone monitoring calls. In the initial assessment, information on risks (age, obesity, nicotine consumption, diabetes, cardiovascular disease, pulmonary disease, chronical hepatic disease, chronical nephrological disease, immunodeficiency, treatment of oncological disease with immunodeficiency, vaccination status), gender, SARS-CoV-2 status, living condition and SARS-CoV-2 status of contact persons, symptom history, legal information (health authorisation, patient decree) is collected and inclusion in the telephone monitoring is defined. The GP individually sets the presumable date of onset of COVID-19 and the extent and frequency of the telephone monitoring. GP-ascertained begin of COVID-19 equals to day 1. GPs are responsible to consider the appropriate monitoring intervals referring to the actual clinical knowledge base regarding the disease course with milestones for deterioration and recovery.

Patients are provided with a monitoring protocol that can be individualized, e.g. for daily log of symptoms and vital signs. The telephone monitoring includes a monitoring of symptoms and signs of infection and the cardio-respiratory system. Individual timelines and figures are created and provide an overview on first symptoms (presumable disease onset), positive test result, disease progression. This aids in assessing the state of health and early detection of a deterioration. A total number of at least three to four contacts is recommended, including the intake, the initial assessment and a closing contact. Any further contacts should be conducted in the critical phase as defined by the knowledge base provided by the RKI [12, 13], the frequency is to be increased with a deterioration. The closing contact includes a short closing documentation not later than three weeks after disease onset. In this closing contact, information on the utilisation of different health care services (e.g. hospitalisation, ventilation) are retrieved and documented.

No further telephone monitorings are conducted when (a) the patient is cured (defined as alive and without symptoms of COVID-19 for 48 h and longer), (b) the patient is hospitalised, (c) the patient has passed away, (d) none of the above has happened not later than three weeks after first symptoms showed.

For patients who are not able to give their informed consent into study participation and where a legal representative gives their informed consent or for patients who are residing in a retirement home or a long-term care institution, the responsible nurse or the responsible legal representative or informal caregivers can document symptoms and vital signs in the monitoring protocol. If none of the above is possible, information can be extracted from existing nursing documentation. For the same groups of patients, the telephone monitoring can be conducted with the responsible nurse or the responsible legal representative or an informal caregiver, if necessary.

The CareCockpit software provides a schedule that allows for systematic follow-ups according to the defined telephone monitoring intervals.

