### Outcomes

The primary outcome is hospitalisation due to COVID-19. The following indicators have been identified as secondary outcomes:

Diagnosis of pneumonia in confirmed and suspected COVID-19 patients [14].Utilisation of palliative care by confirmed and suspected COVID-19 patients during quarantine or stay at hospital.Mortality rate of confirmed and suspected COVID-19 patients (death at home, death in hospital, death in long-term care institution).Anxiety in confirmed and suspected COVID-19 patients using the Generalized Anxiety Disorder Index (GAD-2) [15].Identification of predictive risk factors for the outcomes such as hospitalisation, intensive care and mortality.

For the process evaluation we chose an exploratory sequential design. The process evaluation consists of a qualitative strand and a quantitative strand.

Overall, for the process evaluation we use the RE-AIM framework according to Glasgow and colleagues [16] to assess reach, efficacy, adoption, implementation and maintenance of the CovidCare surveillance and care tool. Table 1 provides an overview of the outcomes, indicators and methods/instruments of the process evaluation according to the RE-AIM framework.

**Table 1 Tab1:** Concept of the process evaluation

Outcomes	Indicators (examples)	Methods/Instruments
1) Reach The extent to which patients are reached by the implementation of CovidCare as well as the number of patients who are willing or refused to participate in CovidCare.	• How have patients been approached • Number of patients approached • Number of patients willing to participate in CovidCare • Patients: Reasons for refusal and drop-out, exclusion rate • Number of contacts per patient (i.e. telephone monitoring, particularly in the critical phase as defined by the RKI as a proxy whether GPs treat their patients according to guidelines) • Characteristics of participating patients	S, I, DB
2) Efficacy The efficacy of the CovidCare-module includes positive and negative impacts/effects for patients and HCP as well as the patients’ quality of life and the patients and the HCP’s satisfaction with the intervention.	• Positive and negative effects on patients’ quality of life, perception of (quality of) care, disease coping • Effects on health care personnel in managing Covid-19 patients • Satisfaction of HCP and patients with CovidCare • Comparison with patients with Covid-19/suspected cases but WITHOUT additional risk factors or aged >50	S, I, DB

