### Statistical methods

#### Statistical methods for primary and secondary outcomes

Data analysis is explorative. Date of the full study population (general practices and patients) will be included in data analysis.

Descriptive statistics of all collected data will be performed. Continuous variables will be described using means, standard deviations, median, minimum, maximum, and first and third quartile. Categorical variables will be reported using absolute and relative frequencies.

The potential effect of sociodemographic characteristics (age, gender, living situation), risk factors (as described above) on the severity of the disease, utilisation of different care services (hospitalisation, intensive care unit, invasive ventilation, palliative care) will be estimated by models taking the clustered structure into account. Therefore, e.g. SAS PROC MIXED, PROC GENMOD or PROC GLIMMIX can be accordingly parametrized to determine fixed and random effects. In order to determine potential differences concerning mortality between particular strata there are also a couple of methods available to take a clustered structure into account. One option is a likelihood-based random effects (frailty) model. The baseline hazard could be either a priori determined (e.g., Weibull) or approximated by piecewise constant counterpart. The estimation could be carried out by adaptive Gaussian quadrature method which is implemented in SAS PROC NLMIXED.

Incubation, begin of the disease, and progression of the disease will be analysed descriptively.

Data analysis for the process evaluation is descriptive and explorative. Qualitative data from interviews will be transcribed according to established standards and will be analyzed with regard to the research questions with qualitative content analysis [17] or framework analysis using the software MAXQDA. Quantitative survey data and the indicators for the intervention fidelity will be analyzed descriptively.

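### The closing record has a three-week ceiling, no earliest date and no named later source, while mortality and in-hospital outcomes carry no time window

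*Protocol article*

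**What the plan says.** All references are to the protocol article.

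- **Intervention description, time origin.** "GP-ascertained begin of COVID-19 equals to day 1".
- **Intervention description, closing contact.** "The closing contact includes a short closing documentation not later than three weeks after disease onset". At this contact, "information on the utilisation of different health care services (e.g. hospitalisation, ventilation) are retrieved and documented". The text gives a latest date and no earliest one.
- **Intervention description, end of calls.** "No further telephone monitorings are conducted when (a) the patient is cured", with cure meaning "cured (defined as alive and without symptoms of COVID-19 for 48 h and longer". Calls also end when "b) the patient is hospitalised, (c) the patient has passed away", or at three weeks after first symptoms if none of these has occurred.
- **Outcomes.** The primary outcome is hospitalisation due to COVID-19. Secondary outcomes include "Mortality rate of confirmed and suspected COVID-19 patients (death at home, death in hospital, death in long-term care institution"), palliative care during quarantine or a hospital stay, and predictors of hospitalisation, intensive care and mortality. None has a time window.
- **Statistical methods for primary and secondary outcomes.** Cluster-aware regression models are planned for disease severity and "utilisation of different care services (hospitalisation, intensive care unit, invasive ventilation, palliative care"). A frailty model is one option for mortality.
- **Plans for assessment and collection of outcomes.** The practice software module is the only data source named for these outcomes.
- **Methods to handle non-adherence and missing data.** No missing values are expected because fields are mandatory, so no imputation is planned.

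**The concern.** Intensive care, ventilation, death in hospital and much of the palliative care occur after admission, sometimes well after it. The plan requires one look at service use, at most three weeks after onset and possibly sooner. For a patient still in hospital at that look, the final outcome is unknown. A mandatory field completed as no would nevertheless enter the dataset as if the event had been ruled out.

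Two things are at stake. First, a mortality or intensive-care rate with no stated window will be read as the eventual rate, although it counts only events up to a closing date that can vary by patient. Second, the study's aim is to estimate risk-factor effects. If time to recovery or time to death differs by age or comorbidity, a contrast between risk groups mixes a difference in risk with a difference in what was observed. An analysis plan cannot recover events that were never collected, so the point belongs in the protocol.

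**Working it through.** The plan states no event rate, event timing, sample size or power, so there is no figure to reproduce. The check is mainly a comparison of the text with itself.

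**Step 1: what is collected against what is to be estimated**

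| Item | Where | What it fixes |
|---|---|---|
| Service-use record | Intervention description | Once, at closing; at most three weeks after onset; no minimum |
| Telephone calls | Intervention description | End at cure, admission, death or three weeks |
| Later outcome source | Plans for assessment and collection of outcomes | None named |
| Mortality | Outcomes | Includes death in hospital; no window |
| Palliative care | Outcomes | Includes the hospital stay; no window |
| Intensive care, ventilation | Statistical methods | Modelled; no window |
| Unknown status at closing | Missing-data section | Not addressed; no missing values expected |

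Two consequences follow.

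1. An event after closing need not be captured.
2. Closing dates may differ between patients. For example, a practice may close a patient declared cured in the second week then, or may wait until week three; the text permits both.

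**Step 2: illustration of size (assumptions, not document figures)**

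Assume that time from onset to death is lognormal with median *m* and log-scale standard deviation *s*. The share of deaths after closing day *c* is

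share = 1 − Φ( ln(*c*/*m*) / *s* ).

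Worked case: *c* = 21, *m* = 14, *s* = 0.6. ln(21/14)/0.6 = 0.405/0.6 = 0.676, and 1 − Φ(0.676) = 0.25.

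| Assumed median (days) | After day 21, *s* = 0.4 | After day 21, *s* = 0.6 | After day 14, *s* = 0.4 | After day 14, *s* = 0.6 |
|---|---|---|---|---|
| 10 | 3% | 11% | 20% | 29% |
| 14 | 16% | 25% | 50% | 50% |
| 18 | 35% | 40% | 74% | 66% |
| 21 | 50% | 50% | 84% | 75% |
| 28 | 76% | 68% | 96% | 88% |

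A gamma distribution with SD 7 or 10 days gives, after day 21, 15–20% (mean 14 days), 30–32% (mean 18) and 48–52% (mean 22). The choice of family matters less than the assumed centre.

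**Step 3: illustration of a biased contrast**

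Take two risk groups with equal eventual mortality (true ratio 1) and assumed median times to death of 14 and 21 days, both closed at day 21. The proportion of deaths seen is Φ(ln(21/14)/*s*) in the faster group and Φ(0) = 0.50 in the slower one. The observed ratio, slower to faster, is:

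- *s* = 0.4: 0.50/0.845 = 0.59
- *s* = 0.6: 0.50/0.750 = 0.67

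This bias needs timing to differ between the groups. The documents do not show whether it does.

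**The case against.** **The list of stopping reasons ends calls, not outcome capture.** This stands. A reader might infer that nothing is recorded after admission or cure. The closing contact is a separate step and can follow either, so intensive care or ventilation before closing can still be retrieved. The firm limit is the three-week ceiling.

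**Unequal follow-up is permitted, not prescribed.** This also stands. Nothing says that closing happens on the day cure is declared.

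**Later events are not necessarily lost.** A reader might infer that every death after three weeks is missed. The documents do not support that. The module holds an end-of-treatment date with reasons and a field for death, data are transferred weekly, and no text says that the record is locked. A practice might enter a later death. But nothing requires it, so such capture could be uneven across practices.

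**The primary outcome is largely spared, and the study is explorative.** This is correct and lowers the severity. Hospitalisation precedes the truncated outcomes and is itself recorded at closing. Only an admission after closing could be missed.

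**A frailty model accommodates different observation times.** This stands in part. It helps mortality only, and only if censoring is unrelated to prognosis, which is doubtful where closing follows cure or admission. The models for service use have no common window.

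**The percentages come from outside the documents.** This stands. They also cover deaths only and put no figure on intensive care, ventilation or palliative care.

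**Labels and censoring rules may be in the full protocol or analysis plan.** They may. But the article itself states the ceiling as a collection rule, and a label cannot supply data that were not collected.

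**Conclusion.** The point holds as one that should be fixed, mainly for the secondary outcomes. The collection rule and the outcome list do not fit together: service use must be recorded once, no later than three weeks after onset and possibly earlier, while mortality, intensive care, ventilation and palliative care are reported or modelled with no window. The likely direction is understatement, because late events in patients still in hospital need not be captured and can appear as non-events. Bias in risk-factor contrasts is possible, conditional on timing that differs between risk groups.

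The size cannot be derived from the documents. The 3% to 76% range for deaths after day 21 rests wholly on the assumed medians (10 to 28 days) and log-scale spreads (0.4 and 0.6). It shows only that the loss could be minor or large.

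**What to change.** Leave the clinical monitoring rules as they are and define the research window.

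1. For every patient, whatever ended the calls, record vital status, hospitalisation, intensive care, ventilation, pneumonia and palliative care as of day 21 after onset. State how day 21 is counted, since the plan sets onset as day 1.
2. Label and analyse these as 21-day outcomes.
3. Report the number still in hospital at day 21. From the practice record, add their status at discharge or death as a separately labelled in-hospital outcome. Do not present this as a longer-term rate for the whole cohort (a 60-day rate, for example): patients who were not in hospital at day 21 would not have been followed to that date, so windows would be mixed again.
4. Do not count patients still in hospital as observed non-events for any outcome extending beyond day 21.

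The cost is one short extra entry for patients closed early, one record look-up for those still in hospital at day 21, and an amendment with an added software field. Practices already transfer data weekly, so the added work is small. Patients whose record has already closed would need the same look-up retrospectively.

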### Criteria for discontinuing or modifying allocated interventions

Not applicable as this is a non-intervention study.

### Strategies to improve adherence to interventions

Not applicable as this is a non-intervention study.

### Relevant concomitant care permitted or prohibited during the trial

Not applicable as this is study does not investigate the use of drugs.

### Provisions for post-trial care

Not applicable as no risks are anticipated for patients and general practices by participating in this study.

### Outcomes

The primary outcome is hospitalisation due to COVID-19. The following indicators have been identified as secondary outcomes:

Diagnosis of pneumonia in confirmed and suspected COVID-19 patients [14].Utilisation of palliative care by confirmed and suspected COVID-19 patients during quarantine or stay at hospital.Mortality rate of confirmed and suspected COVID-19 patients (death at home, death in hospital, death in long-term care institution).Anxiety in confirmed and suspected COVID-19 patients using the Generalized Anxiety Disorder Index (GAD-2) [15].Identification of predictive risk factors for the outcomes such as hospitalisation, intensive care and mortality.

For the process evaluation we chose an exploratory sequential design. The process evaluation consists of a qualitative strand and a quantitative strand.

Overall, for the process evaluation we use the RE-AIM framework according to Glasgow and colleagues [16] to assess reach, efficacy, adoption, implementation and maintenance of the CovidCare surveillance and care tool. Table 1 provides an overview of the outcomes, indicators and methods/instruments of the process evaluation according to the RE-AIM framework.

**Table 1 Tab1:** Concept of the process evaluation

Outcomes	Indicators (examples)	Methods/Instruments
1) Reach The extent to which patients are reached by the implementation of CovidCare as well as the number of patients who are willing or refused to participate in CovidCare.	• How have patients been approached • Number of patients approached • Number of patients willing to participate in CovidCare • Patients: Reasons for refusal and drop-out, exclusion rate • Number of contacts per patient (i.e. telephone monitoring, particularly in the critical phase as defined by the RKI as a proxy whether GPs treat their patients according to guidelines) • Characteristics of participating patients	S, I, DB
2) Efficacy The efficacy of the CovidCare-module includes positive and negative impacts/effects for patients and HCP as well as the patients’ quality of life and the patients and the HCP’s satisfaction with the intervention.	• Positive and negative effects on patients’ quality of life, perception of (quality of) care, disease coping • Effects on health care personnel in managing Covid-19 patients • Satisfaction of HCP and patients with CovidCare • Comparison with patients with Covid-19/suspected cases but WITHOUT additional risk factors or aged >50	S, I, DB
3) Adoption Adoption refers to the number of HCP and practices who agree to use the CovidCare-module and aims to understand the reasons for (not) participating in the intervention.	• Reasons for (not) participating in CovidCare; comparing characteristics of participants and non-participants (HCP, practices and patients) • Characteristics of participating HCP and practices • Barriers and facilitators	I, S, DB
4) Implementation Implementation refers to the extent to which CovidCare is used delivered as intended.	• Problems, time, and cost of the intervention • Adaptions that were necessary to implement/use CovidCare in daily practice	I, S, DB
5) Maintenance The extent to which the CovidCare-module became part of the daily practice routines of the individual HCP and the GP’s practice.	• Factors that facilitate the uptake of the intervention/ implementation into routine care • Suggestions for improving the intervention in order to enable CovidCare to become part of organizational practice	I

*DB* database, *HCP* health care personnel, *I* interviews, *S* survey

### Participant timeline

Development of study material, such as assessments, and software programming has started in March 2020. The CovidCare-module is available for eligible general practices since April 30th 2020. Patient recruitment for this study in the general practices can start as soon as the software has been installed and activated. Data collection ends on December 31st 2021. The process evaluation will start in March 2021. All patients whose COVID-19 disease have been cured will be invited to participate in an interview and in the questionnaire survey after the final consultation. Patients willing to participate in the process evaluation will be contacted by the study team via telephone to get more information about the study, answer open questions and schedule an interview and send the questionnaire to the patient. Interviews will take place in a timely manner after the patient provided his/her written informed consent. Evaluation, data analysis and publication are planned to be conducted continuously. If the COVID-19 pandemic persists or becomes active again the study may be prolonged after positive verification of an amendment to the ethics committee. In this case the practices have to reactivate the software with a new key after re-registration.

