### Trial status

Protocol version number: 1.4, date: 19th May 2021.

Date the recruitment began: 30th April 2020.

The approximate date when recruitment will be completed: 31st December 2021.

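### Recruitment and data collection both end on 31 December 2021, so patients with onset after about 10 December who are unresolved at that date may lack a complete primary outcome

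*Protocol article*

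**What the plan says.** Two end dates are given. The Participant timeline section has "Data collection ends on December 31st 2021". The Trial status section has "The approximate date when recruitment will be completed: 31st December 2021", and for the start, "Date the recruitment began: 30th April 2020".

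The Outcomes section states: "The primary outcome is hospitalisation due to COVID-19". The Intervention description says when and how this is documented. The clock starts at onset ("GP-ascertained begin of COVID-19 equals to day 1"), and the end point is a closing contact: "The closing contact includes a short closing documentation not later than three weeks after disease onset". It continues: "In this closing contact, information on the utilisation of different health care services (e.g. hospitalisation, ventilation) are retrieved and documented". Monitoring can stop sooner: "No further telephone monitorings are conducted when (a) the patient is cured", and likewise on hospital admission or death.

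The article sets no period of continued data collection after the last enrolment. The Participant timeline section allows the study to be prolonged, but only if the pandemic persists or returns and only after an ethics amendment. The section on non-adherence and missing data expects complete data sets because fields are mandatory, rules out imputation on that ground, and allows a non-responder analysis if one is needed.

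**The concern.** A patient can be enrolled on the last day of recruitment, yet the contact at which hospitalisation is documented may fall due up to three weeks after onset. If data collection closes on that same last day, some late patients reach the cut-off with their outcome still open.

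The patients cut off are not a random subset. Among those with onset in the final weeks, quick recoveries and quick admissions are resolved before the cut-off. Patients still symptomatic at home are not, and their later admissions would be missed. Incompleteness would then depend on disease course and on calendar time, and disease course is what the risk-factor models are meant to explain. A patient admitted shortly before the cut-off has a known primary outcome, but intensive care, invasive ventilation, palliative care or death in hospital may still lie ahead.

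A mandatory field ensures that something is entered. It cannot supply an event that has not yet happened, so the complete-data statement does not deal with this truncation.

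**Working it through.** The plan gives no figure of its own to reproduce here, so the check is calendar arithmetic on its stated dates.

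**Inputs**
- Start of recruitment: 30 April 2020 (Trial status).
- End of recruitment: 31 December 2021, approximate (Trial status).
- End of data collection: 31 December 2021 (Participant timeline).
- Maximum time from onset to closing contact: three weeks, or 21 days (Intervention description).
- Lag from onset to enrolment: not given. I assume a range of 0 to 14 days.

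**Length of recruitment**
30 April 2020 to 30 April 2021 is 365 days, and 30 April 2021 to 31 December 2021 is 245 days. Counting both end dates: 365 + 245 + 1 = 611 days.

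**Latest onset with a full window**
31 December 2021 − 21 days = 10 December 2021. If onset counts as day 1 and day 21 is the last day, the result is 11 December. Hence "about" 10 December is as exact as the text permits.

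**Enrolment days without a full window**
The window runs from onset, so a patient enrolled some days after onset has already used part of it. Exposed enrolment days = 21 − lag, and share = (21 − lag) / 611.

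| Lag, onset to enrolment (assumed) | Exposed enrolment days | Share of recruitment period |
|---|---|---|
| 0 days | 21 | 3.4% |
| 5 days | 16 | 2.6% |
| 7 days | 14 | 2.3% |
| 10 days | 11 | 1.8% |
| 14 days | 7 | 1.1% |

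These are shares of calendar time. They equal shares of patients only under even accrual. They are also taken before removing patients whose monitoring ends early through cure, admission or death, so under even accrual the share of patients with an open outcome is lower than the table shows.

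**Date that would close the gap**
If recruitment stays open to 31 December 2021 and onset falls on or before enrolment, the last window closes on 31 December 2021 + 21 days = 21 January 2022.

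**The case against.** The strongest reply is that the gap is narrow and partly covered already. Most of its elements stand.

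- **The window is not three weeks from enrolment.** A reader might infer that nobody enrolled in the last three weeks can complete follow-up. The text does not support that. The clock starts at onset, so a patient enrolled on 15 December with onset on 8 December has the full window. Three weeks is also a ceiling: a patient cured by day 10 can be closed out well before day 21.
- **Nothing says that open records count as event-free.** A reader might infer this from the complete-data statement, but the article fixes no such rule. It lists end of treatment, with date and reasons, among the recorded items, so an open record can be identified. It also names loss to follow-up and allows a non-responder analysis.
- **Some events are captured anyway.** Admission itself ends monitoring, death is among the monitoring items, and transfer is weekly. Events before the cut-off may be known without a closing contact; later ones are lost. For mortality, the frailty model named as an option can handle censoring.
- **Outstanding consent makes late patients absent, not wrongly coded.** Nothing is transferred until signed consent is received, so some of the last recruits may not appear in the data at all.
- **A figure near 10% has no basis in the article.** It would take threefold accrual in the last 21 days: 63 / (611 + 42) = 9.6%. The article gives no accrual rate, and that calculation again counts every late enrolee as truncated.
- **The process evaluation is hardly touched.** Its patient interviews are planned for about 20 people, and the process evaluation starts in March 2021.

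Two elements do not stand. The word approximate in the recruitment date and the conditional prolongation do not create a follow-up tail; if both dates move together, the same gap reappears. Nor is this a detail that a condensed article may leave to a fuller document: the article states both dates and the follow-up length, and they do not fit together.

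**Conclusion.** The point holds in limited form. As written, the plan leaves no time after the last enrolment for outcomes to be documented. The patients exposed are those with onset after about 10 December 2021 who have not been cured, admitted or died by 31 December. Those admitted in late December are exposed for the outcomes that follow admission.

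In calendar time, at most about 3.4% of the recruitment period is affected, and about 1% to 3% if enrolment lags onset by 5 to 14 days. That range rests on an assumed lag. Reading it as a share of patients also assumes even accrual, which the article does not promise: its Sample size section says numbers depend on uncertain incidence. If accrual is concentrated in December 2021, the share rises by an amount that cannot be derived from the article.

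For an exploratory analysis the likely effect is small. The correction is still worth making, because the truncation touches the primary outcome, is related to disease course, and costs little to remove. The direction of any bias cannot be fixed in advance. Counting open records as not hospitalised would under-count admissions. Dropping only the open records would keep the quickly resolved courses from the same weeks and lose the slower ones.

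**What to change.** Separate the two dates, in one of two ways:

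1. Keep recruitment to 31 December 2021 and let closing contacts and weekly data transfer continue to at least 21 January 2022. Choose a later date if outcomes after admission are to be followed beyond the three-week window, or to allow for consent forms still in the post.
2. Keep 31 December 2021 as the end of data collection and limit the analysis set to patients with onset on or before about 10 December 2021. The limit should be set by onset date, not by whether the record happens to be closed, so that selection does not depend on disease course.

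Under either option, state that a record still open at the cut-off is incomplete: censored in a time-to-event analysis, and not entered as event-free in a model for a binary outcome. Add a sentence to the missing-data section saying that mandatory fields do not cover this case.

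The first option costs a changed date, an ethics notification and a few more weekly transfers. The second costs the loss of a few late patients.
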